### Child-interview intervention vs. adult-only intervention in AMK investigation

All reports to an AMK are discussed in a multidisciplinary team meeting which draws up a plan for the investigation. It is at this team meeting that the choice of AMK investigation with or without the Child-Interview intervention is made, based on information from the person who reported the alleged maltreatment.

### AMK investigation without child-interview intervention

If the multidisciplinary team decides on AMK investigation without the intervention, only adults will be approached for information. The multidisciplinary team will decide which adults should be approached. Usually, the parents, teacher(s) and family doctor are part of this investigation, but other adults such as family members, social workers, therapists, or healthcare specialists can also be approached, depending on the social environment of the reported child/family. Information will be collected by phone, email contact or by a home visit.

### AMK investigation including the child-interview intervention

In addition to information from adults (see above), the child and his/her siblings will be asked as informants. The Child-Interview intervention comprises the child being interviewed by an AMK employee. This interview takes place at the child’s home or at school, in a separate room. The duration of the interview depends on the child’s needs. The aim of the interview is for the AMK employee to discover if there are problems in the family or its surroundings, if the child needs care and what type of care would be suitable. An additional aim is to increase the child’s sense of being in control.

The Child-interview intervention used by the AMKs is part of the investigation to substantiate a report of suspected child maltreatment and to identify the needs for child and family care. It does not serve a forensic purpose.

### Outcome measures

#### (1) Effectiveness study

##### Mental health

Children’s mental health (in terms of internalizing and externalizing psychological problems) as observed by the parents, will be measured with the Dutch version of the Child Behavior Checklist (CBCL) [38]. Parents will be asked to what extent they observe various behavioral and emotional problems in their child. The CBCL uses a 3-point scale and consists of 113 items. Internal consistency is good (α .97) [38].

##### Quality of life

Children’s quality of life will be measured with one of three age-appropriate versions (5–7, 8–11, 12–18 years) of the Dutch translation of the Pediatric Quality of Life Inventory (PedsQL) [39]. Children will be asked to express their concerns on the dimensions of physical health and psychosocial health, the latter consisting of the subdimensions of emotional functioning, social functioning and school functioning. The overall quality of life score will be obtained by adding up the scores on all dimensions. The PedsQL uses a 5-point scale (or a 3-point scale for the 5–7 version) and consists of 23 items. Internal consistency is good (α .82- .85) [39].

#### (2) Economic evaluation study

##### Societal costs

Healthcare costs of the child and the family will be measured using an adapted version of the Trimbos Institute Medical Technology Assessment Cost Questionnaire for Psychiatry (TiC-P) [40]. This questionnaire will be completed by the parent. As the TiC-P is not completely suitable for this intervention, the TiC-P had to be adapted, using a bottom-up approach. In this procedure, AMK managers and AMK workers were asked to review the TiC-P for the purpose of studying a maltreated population and they were asked to add services that families that are reported to an AMK use regularly and that were missing from the TiC-P. This resulted in a suitable questionnaire to record societal costs of maltreated children and their families. The updated version of the TiC-P questionnaire included the following services: general practitioner, company doctor, first aid post at hospital, medical specialist at hospital, hospitalization (including general hospital, psychiatric hospital, rehabilitation center, university hospital), psychiatrist/psychologist/psychotherapist working at hospital, psychiatrist/psychologist/psychotherapist with private practice, physical therapist, alternative healer (e.g. homeopathy), self-help group therapy, child welfare service on outpatient basis, child welfare service as day care, child welfare service on inpatient basis, AMK, youth and family center, infant welfare center, regional public health service, home care, personal care budget (allocated by local government), social worker, school (including school doctor, compulsory education officer), police, probation service, addiction service, financial assistance, and lawyer/legal aid.

Costs will be valued on the basis of guideline prices derived from the updated Dutch manual for cost analysis in healthcare research [41]. As the guideline only includes healthcare costs, costs outside the healthcare sector will be valued separately.

### Quality adjusted life years (QALYs)

An increased quality of life is expressed as a *utility* value on a scale from 0 (death) to 1 (perfect quality of life). In health economics, utilities are combined with survival estimates and aggregated across individuals to generate quality adjusted life years (QALYs). A one-year increase in the duration of life (without change in quality of life), or an increase in quality of life from 0.5 to 0.7 utility units for five years, would both result in a gain of one QALY. Children’s QALYs will be derived from a thermometer question. Children will be asked to answer the question: “*On a scale from 1 to 10, how healthy did you feel over the past 6 months?”* The scores will be converted to utility scores by dividing by 10, obtaining a score between 0.00 and 1.00. The change in utility value between the two assessment points will be multiplied by the duration of the intervention effect to obtain the number of QALYs gained.

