## Design/methods

### Study design

To answer the research questions, a quasi-experiment will be performed in which respondents from an ongoing prospective study on the mental health and quality of life of maltreated children after a report to an AMK [35] will be asked to complete an additional questionnaire at follow-up assessments. The quasi-experiment will consist of two post-intervention assessments of two nonequivalent groups (intervention group and control group) (see Figure 1). The study sample of the prospective study consists of maltreated children and their primary caretaker. These parent–child dyads were recruited for participation in the prospective study during the AMK investigation following a report to an AMK. Based on information from AMK records, the study sample will be divided into two groups: an intervention group, in which the Child-Interview intervention was used during the AMK investigation, and a control group, in which the intervention was not used (adult-only intervention).

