**Figure 1 F1:**
[figure not shown]
**Flow chart of quasi-experimental study design.***Note. Assessment 1 and 4 of the prospective study have no connection with the quasi-experiment.*

The gold standard for experimental and effectiveness and cost-effectiveness studies is a randomized controlled trial (RCT), in which participants are divided to two study groups based on random assignment. The Dutch Medical Ethics Committee for Mental Health Care (METiGG) did not approve of a RCT, because randomization might result in a parent–child dyad receiving a suboptimal approach (in this case the adult-only intervention), which the committee decided was not ethically acceptable in the case of vulnerable young children. Although evidence on the adult-only intervention is lacking, this is supported by Article 33 of the Declaration of Helsinki. This article states that it is not acceptable to withhold treatment/intervention when it is known that this treatment can be lifesaving or that abstinence might lead to irrecoverable damage to the subject [36].

While preparing for the study, however, we found from AMK records that although the Child-Interview intervention is the preferred method according to the AMK manual [13], the Child-Interview intervention was not used during the investigation in a substantial number of AMK investigations. This enabled us to propose a quasi-experimental design in which an existing study sample (from the prospective study mentioned above) was divided into two groups based on the intervention they had received during the AMK investigation. Data collection for the quasi-experiment could be incorporated in this prospective study (see Figure 1). This design would make it possible to answer the research questions without randomization, though a disadvantage of this design is the possibility of selection bias. The economic evaluation will involve a combination of a cost-effectiveness analysis (CEA) and a cost-utility analysis (CUA).

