### Assessment

This study will consist of two assessments: A and B (see Figure 1). Assessment A will take place at the same time as assessment 2 of the prospective study (6 months after the AMK investigation). Assessment B will take place six months later, at the same time as assessment 3 of the prospective study (12 months after the AMK investigation).

At assessments A and B, children and parents will be asked to complete a questionnaire. A member of the research team will meet the parent and child at a place of their choice (in most cases their own home) to assist them. The way in which the questionnaire is to be completed will be discussed with the parent and the child, and will depend on the participants’ reading and writing skills. If reading and writing skills are poor, a research team member will read out the questions and write down the participant’s answer on the questionnaire form. If reading and writing skills are sufficient, participants may choose to complete the questionnaire by themselves. To prevent the parents from influencing the children’s answers, parents and children will be requested to complete their questionnaires in separate rooms. Respondents will be rewarded for their participation by a 10 euro gift voucher for the parents, while the children will receive either a 5 euro gift voucher (children > 10) or an age-appropriate present (6–10 years).

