#### (2) Economic evaluation study

In this study, additional costs and additional outcomes of the Child-Interview intervention will be compared with those of the adult-only intervention. The incremental cost-effectiveness ratio (ICER) will be expressed as the incremental costs per degree of improvement in mental health of the Child-Interview intervention group in comparison with the control group (adult-only intervention). The incremental cost-utility ratio (ICUR) will be expressed as the incremental costs per QALY of the Child-Interview intervention group in comparison with the control group (adult-only intervention).

The ICER (and ICUR) will be calculated using ICER = (Ci-Cc)/(Ei-Ec), where Ci is the annual total costs of the Child-Interview intervention, Cc the annual costs of the adults-only intervention, Ei the effect at 6-months follow-up for the Child-Interview intervention and Ec the effect at 6-months follow-up of the adult-only intervention. The robustness of the ICER will be checked by non-parametric bootstrapping (1000 times). The bootstrap replications will be used to calculate 95% confidence intervals around the costs. The bootstrapped ratios (ICER and ICUR) will be graphically presented in two ways: (1) plotted in a cost-effectiveness plane, in which the vertical line reflects the difference in costs and the horizontal line reflects the difference in effects, and (2) in a cost-effectiveness acceptability curve, showing the probability that the Child-Interview intervention is cost-effective based on a range of ceiling ratios (the maximum amount of money society is willing to pay to gain one extra unit of effect or a gain in QALY). Additionally, the robustness of the base-case findings will be assessed using a sensitivity analysis [42]. This economic evaluation will be performed from a societal perspective. Bootstrapping will be carried out in Excel.

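### QALYs gained are defined as the change between two post-intervention assessments, so a utility difference already recorded at month 6 and maintained counts as zero, and one that fades counts as a loss

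*Protocol article*

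**What the plan says.** The section on quality adjusted life years derives utility from one thermometer item, which asks the child "how healthy did you feel over the past 6 months" on a scale from 1 to 10. The score is divided by 10. QALYs gained then follow from this rule: "The change in utility value between the two assessment points will be multiplied by the duration of the intervention effect". No value is given for that duration. The same section illustrates a QALY with a utility rise from 0.5 to 0.7 that lasts five years.

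The timing is fixed elsewhere in the article:

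- Study design: "The quasi-experiment will consist of two post-intervention assessments of two nonequivalent groups".
- Assessment: "Assessment A will take place at the same time as assessment 2 of the prospective study (6 months after the AMK investigation"); assessment B comes six months later, "at the same time as assessment 3 of the prospective study (12 months after the AMK investigation").
- Note to Figure 1: "Assessment 1 and 4 of the prospective study have no connection with the quasi-experiment".

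In the economic evaluation part of the Analyses, the incremental ratio is the cost difference over the effect difference, for the ICER and the ICUR alike. On the cost side, "Ci is the annual total costs of the Child-Interview intervention". On the effect side, the formula takes the effect at the six-month follow-up in each group.

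**The concern.** A QALY gain is utility above the level expected without the intervention, accumulated over time. The article's own example has that form. The rule for this study does not: it subtracts the first post-intervention value from the second, as if A were a pre-intervention baseline. Whatever effect the score at A already contains is subtracted out.

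The result is the denominator of the ICUR. If it is zero for a beneficial intervention, the ratio is undefined. If it is negative, the ratio takes the wrong sign, and raising the ceiling ratio makes the intervention look less acceptable. There is also a mismatch of periods: the numerator is a year of costs, while the denominator compares the second half-year with the first and does not accumulate utility over the year.

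**Working it through.** **The article's own example.** Utility gain × years = (0.7 − 0.5) × 5 = 1.0 QALY, as stated. The gain is an elevation over a no-effect level, multiplied by the time it is held.

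**Inputs.** A is at month 6 and B at month 12 (Assessment). Each item looks back six months, so A covers about months 0–6 and B about months 6–12. The article gives neither the utility differences nor T. The differences below are illustrative, and T is assumed to lie between 0.5 and 1 year.

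**Formulas.** Let dA and dB be the between-group differences (Child-Interview minus adult-only) in utility at A and B.

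- Rule in the article: incremental QALY = (dB − dA) × T. A trend common to both groups cancels.
- Twelve-month area, using the two recall windows: 0.5 × dA + 0.5 × dB.

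**Results, assuming the groups would not differ without the intervention.**

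| Pattern (dA, dB) | Rule, T = 0.5 | Rule, T = 1 | 12-month area |
|---|---|---|---|
| Maintained (0.05, 0.05) | 0 | 0 | 0.05 |
| Fading (0.10, 0.05) | −0.025 | −0.05 | 0.075 |
| Fully faded (0.10, 0) | −0.05 | −0.10 | 0.05 |
| Gradual build-up (0.05, 0.10) | 0.025 | 0.05 | 0.075 |
| Early deficit, recovered (−0.10, 0) | 0.05 | 0.10 | −0.05 |

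For example, in the fading row (0.05 − 0.10) × 0.5 = −0.025 and (0.05 − 0.10) × 1 = −0.05, against 0.5 × 0.10 + 0.5 × 0.05 = 0.075. The maintained row is zero for every T. The gradual row is a benefit that rises linearly to 0.10 at month 6 and then holds: averaged over the recall window it shows as 0.05 at A and 0.10 at B. The last row shows that an early harm that resolves is credited as a gain.

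**Does the sign depend on the choice of area?** A trapezoid over 0–12 months with the groups equal at month 0 is 0.25 × dA + 0.25 × (dA + dB). It gives 0.0125 + 0.025 = 0.0375 for the maintained row and 0.025 + 0.0375 = 0.0625 for the fading row. A trapezoid from A to B only, 0.25 × (dA + dB), gives 0.025 and 0.0375. All are positive, where the rule gives zero or a loss.

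**Allowing for selection.** Write dA = g + eA and dB = g + eB, with g a stable selection gap and eA, eB the effects. The target is 0.5 × (eA + eB). The rule gives (eB − eA) × T: g cancels, but at T = 0.5 the result misses the target by exactly eA. The area gives g + 0.5 × (eA + eB): it keeps the effect and carries g as bias.

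**The case against.** The strongest objection concerns the comparator. The groups are nonequivalent, and the Discussion gives reasons why they may differ from the start: parental refusal, a child already seen by a professional, language barriers. The pattern (0.05, 0.05) could come from a constant gap of 0.05 with no effect at all. The rule would then correctly return 0, and the area would return a false 0.05. A change score cancels stable differences; a difference in levels does not. This stands. It means that the area figures are the true gain only without a selection gap, and that covariate adjustment cannot fully help because no pre-intervention utility exists. It does not rescue the rule: A lies six months after the investigation, so subtracting it removes effect together with selection, and the remainder is still not a quantity of QALYs gained.

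Second, a reader might infer that every benefit reached by month 6 and then held is scored as zero. The documents do not support that. The item looks back six months, and the proposed mechanism, referral to better tailored care, may take time. A gradual benefit is then only partly visible at A, and the rule understates it (0.025 to 0.05 against 0.075). Exact zero requires equal recorded differences at A and B.

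Third, a reader might infer that the acceptability curve always points the wrong way. That fits the fading case. With an incremental QALY of zero, the comparison rests on the cost difference alone.

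Fourth, the ratio formula's effect at the six-month follow-up could be read as a level at one time point. For the ICUR, however, the effect is the QALY, and the QALY section defines that as a change. At best the two places disagree and need to be reconciled.

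Finally, the missing value for the duration may be given in a fuller plan and is not held against the article.

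**Conclusion.** The point holds for the incremental QALY and so for the ICUR. As written, the denominator is (dB − dA) × T, built from two post-intervention scores. It is zero when the recorded difference is maintained, negative when it fades, and too small when the benefit builds up gradually over months 0–6 (for T of 0.5 to 1 year). The article's own example treats a gain as utility held over time, and the rule does not measure that. It is also set against annual costs.

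The illustrative size is 0 instead of 0.05 QALY for differences of 0.05 and 0.05, and −0.025 to −0.05 instead of 0.075 QALY for 0.10 and 0.05. These figures assume no selection difference, T between 0.5 and 1 year, and answers that average over the recall window. The utility differences are assumptions, and the results scale linearly with them.

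The scope is limited. The effectiveness comparison at B and the ICER for mental health do not use QALYs, so the primary aim is untouched.

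**What to change.** 1. In the QALY section, define each child's 12-month QALYs as 0.5 × utility at A + 0.5 × utility at B. The two recall windows together cover the year to which the costs refer.
2. Use the covariate-adjusted between-group difference in that quantity as the ICUR denominator.
3. Take the multiplication by effect duration out of the base case. Any effect assumed to last beyond 12 months belongs in a labelled scenario.
4. In the economic evaluation section, reconcile the effect term of the ratio formula with this definition for the ICUR.
5. State the limitation next to the result: with no pre-intervention utility, a difference in levels does not cancel stable selection differences between the groups. The A-to-B change may be reported as a sensitivity analysis, but not as QALYs gained.

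The cost is a few sentences in two sections; both thermometer scores are already planned. The price in interpretation is that the new base case is exposed to stable selection differences that the change score would cancel, which is why item 5 is part of the fix.

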### Analyses

Data will be analyzed according to the intention-to-treat principle. The similarity of baseline characteristics (socio-demographic characteristics, costs and outcomes) between the two AMK investigation interventions will be examined using univariate tests and Chi-square tests. Loss-to-follow up will be accounted for by imputing missing data using regression imputation.

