### Sample size and recruitment

Participants from an ongoing prospective study on the mental health and quality of life of maltreated children after a report to an AMK [35] will be contacted to complete assessments A and B (see Figure 1). Parents and children will be asked to give written informed consent for their participation. Five dyads from the sample of this prospective study were excluded because they did not meet age criteria, while for 22 parent–child dyads maltreatment was not verified during the AMK investigation and for 17 dyads the type of maltreatment did not meet inclusion criteria of the quasi-experiment. Hence, the study sample for the present quasi-experiment will include 117 parent–child dyads. A sample size calculation confirmed that this is a sufficient number of participants. Based on the ability to detect a medium effect size or larger clinical effect (Cohen’s d > 0.45) [37] and tested at a conventional power of (1-beta) 0.80 and alpha of 0.05 (one-tailed testing), a total number of 110 parent–child dyads is required.

Supported by AMK records, this sample will be split up into two groups: an intervention group, in which the Child-Interview intervention was used during the AMK investigation, and a control group, in which the intervention was not used (adult-only intervention).

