#### (1) Effectiveness study

A multivariate regression analysis will be performed in which outcomes of mental health and quality of life will be compared between the Child-Interview intervention group and the control group (adult-only intervention). This will be done at follow-up (assessment B), 6 months after assessment A and a year after the intervention. Covariates will be taken into account.

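### Loss to follow-up is handled by unqualified regression imputation, with nothing that carries imputation uncertainty into the group tests, cost intervals or acceptability curve

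*Protocol article*

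**What the plan says.** In the protocol article, the opening paragraph of Analyses gives the whole missing-data rule: "Loss-to-follow up will be accounted for by imputing missing data using regression imputation". The number of imputations, the variables in the imputation model, any random residual and any pooling rule are not mentioned there or elsewhere in the article.

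The completed data then serve two purposes:

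- **Effectiveness.** Analyses, (1) Effectiveness study: "A multivariate regression analysis will be performed in which outcomes of mental health and quality of life will be compared" between the two groups. On timing: "This will be done at follow-up (assessment B), 6 months after assessment A and a year after the intervention". On adjustment: "Covariates will be taken into account".
- **Economic evaluation.** Analyses, (2) Economic evaluation study plans 1,000 non-parametric bootstrap replications, run in Excel: "The bootstrap replications will be used to calculate 95% confidence intervals around the costs". The same replications feed the cost-effectiveness plane and the acceptability curve. The sensitivity analysis mentioned there concerns the economic base case and is not tied to missing data.

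Sample size and recruitment sets alpha at 0.05, one-tailed, and counts 117 available dyads. No expected loss to follow-up is given.

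**The concern.** Regression imputation in its plain form replaces each missing value with its prediction from a fitted regression. The filled-in values have no residual scatter, and the uncertainty of the fitted coefficients is ignored. An analysis that counts them as real observations uses a residual variance that is too small and a sample size that is too large, so standard errors shrink twice over. This happens even when data are missing completely at random.

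At stake are the validity of the group comparison on mental health and quality of life, and the confidence attached to the cost-effectiveness results. The article's closing discussion expects the study to inform the choice of investigation approach and points to policy makers' interest in such evidence.

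**Working it through.** **Inputs from the article.** 117 dyads and one-tailed alpha 0.05 with d = 0.45 (Sample size and recruitment). About 40% adult-only investigations (Discussion), so 0.60 × 117 ≈ 70 against 47.

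**Assumptions.** Loss m of 6%, 10%, 20% and 30%; correlation between assessments A and B of 0.3 to 0.6; values missing completely at random. The 6% is the margin between available and required dyads, (117 − 110)/117 = 7/117.

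**The plan's own figure.** There is no stated loss rate, standard error or error rate to reproduce. The nearest figure is the requirement of 110 dyads. The usual formula gives 2 × (1.645 + 0.842)² / 0.45² ≈ 61.1, so 62 per group and 124 in total; 110 is not reproduced. That is a separate matter and nothing below depends on it.

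**Step 1: closed form, group and analysis covariates in the imputation model.** Imputed points lie on the fitted surface, so the group estimate equals the complete-case estimate. The residual sum of squares is unchanged but is divided by about n instead of (1 − m)n. The inverse design matrix shrinks by another factor of about (1 − m). The reported variance is therefore about (1 − m)² times the true one, which gives:

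- reported SE / true SE ≈ 1 − m
- one-tailed error ≈ 1 − Φ(1.645 × (1 − m)); at m = 0.20, 1 − Φ(1.316) = 9.4%
- coverage of a 95% interval ≈ 2Φ(1.96 × (1 − m)) − 1

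**Step 2: simulation under no true effect.** 117 dyads (70:47), correlation 0.6, 6,000 runs per setting. Single imputation is from group and A. Multiple imputation uses 20 sets and Rubin's rules, analysed with A as covariate.

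| Assumed loss | SE ratio (closed form) | One-tailed error (closed form) | 95% coverage (closed form) | Simulated error, A as covariate | Simulated error, A not a covariate | Multiple imputation |
|---|---|---|---|---|---|---|
| 6% | 0.94 | 6.1% | 93.5% | – | – | – |
| 10% | 0.90 | 6.9% | 92.2% | 6.5% | 6.3% | 4.7% |
| 20% | 0.80 | 9.4% | 88.3% | 9.5% | 7.4% | 5.0% |
| 30% | 0.70 | 12.5% | 83.0% | 13.3% | 9.9% | 5.2% |

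With correlation 0.3 and 20% loss, the simulated error is 9.2% (A as covariate) or 8.7% (not). Separate runs at 6% loss gave 5.6–6.0%. Rounded over settings, the error is about 5–6%, 6–7%, 8–10% and 10–13%; the 7.4% cell lies just below its range.

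Adding a random residual but still imputing only once does not repair this: 6.5%, 8.4% and 11.1% at 10%, 20% and 30% loss.

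**Step 3: group left out of the imputation model.** Simulated one-tailed error over 6–30% loss lies between 4.6% and 5.8%, so the test keeps its size. But the imputed values then carry no group difference of their own. If A shows no group difference either, the expected estimate is about (1 − m) × d = 0.80 × 0.45 = 0.36 at 20% loss, in line with the simulated value of about 0.35. If A already shows the full difference, part is recovered through A: about 0.36 + 0.20 × r × 0.45, which is 0.39 at r = 0.3 and 0.41 at r = 0.6.

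**Step 4: costs.** Lognormal costs (log-SD 1 and log-scale correlation 0.5, both assumed) were imputed once and then bootstrapped. Coverage of the 95% interval for the cost difference fell from 93.5% with complete data to roughly 89%, 85% and 80% at 10%, 20% and 30% loss. These figures shift by a few points with the details of the set-up. An acceptability curve from the same replications would be too steep for the same reason.

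**The case against.** **The text does not say "single".** Nor does it say that imputed values are analysed as if observed. The term could cover stochastic or repeated regression-based imputation, and a condensed article may leave such details to a fuller document that is not shown. This stands as a caution: the point rests on the ordinary meaning of an unqualified term. It does not remove the point, because the article names a method and plans no pooling step, and a single imputation with random residuals also fails.

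**The direction of the harm depends on an unstated choice.** A reader might infer that the false-positive rate is inflated whatever the imputation model. The article does not support that. Inflation needs group in the model; without it, the harm is attenuation. This stands.

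**Loss may be low.** The Assessment section describes assisted visits at a place of the family's choice and rewards for parent and child. These do not guarantee low loss, but at 6–10% the effect is minor. This stands.

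**Costs.** A reader might infer that skewed costs suffer most because imputed values have no tail. The calculations do not bear this out: with lognormal outcomes and an ordinary regression test at 20% loss, coverage is 88–90% against 89–90% for normal outcomes, and one-tailed error 8.3–9.5% against 7.5–9.4%. The article also does not state the order of imputation and bootstrapping, so the overconfidence in Step 4 applies if imputation is done once beforehand.

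**Conclusion.** The concern holds in conditional form. On its ordinary reading, the stated rule is single imputation followed by analysis as if the data were complete, and either version of the imputation model is unsatisfactory:

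- **Group included:** standard errors are too small. The one-tailed 5% test runs at about 5–6%, 6–7%, 8–10% and 10–13% for losses of 6%, 10%, 20% and 30%, so it is minor at low loss and roughly doubled at 20–30%.
- **Group omitted:** the error rate stays near 5%, but a true d of 0.45 shrinks to about 0.35 at 20% loss, or less severely if assessment A already shows the group difference.

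Bootstrapping once-imputed data would make the cost intervals and acceptability curve too confident.

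All of this rests on assumed loss rates and on values missing completely at random; informative loss would add bias beyond what is shown. Because the size runs from negligible to substantial on facts the article does not give, this is a should-fix. The documents do not support calling it fatal to the analysis.

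**What to change.** Replace the sentence in Analyses with multiple imputation, for example 20 or more sets. Put study group, assessment-A outcomes and costs, and the analysis covariates in the model, use predictive mean matching for costs, and pool by Rubin's rules. For CBCL and PedsQL, a mixed model on all observed A and B data is an alternative.

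For the economic evaluation, combine imputation with the bootstrap, for example by imputing within each bootstrap sample, so that the cost intervals, the plane and the acceptability curve reflect imputation uncertainty.

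Assessment-1 values are optional auxiliary variables only, since the note to Figure 1 separates that assessment from the quasi-experiment. If multiple imputation was intended all along, it is enough to say so and state the number of sets, the model content and the pooling rule.

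Cost: no new data and modest extra analysis work. The bootstrap would have to move from Excel to statistical software, and the intervals will be wider.
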